**Secondary outcomes:**

Secondary outcomes include mortality from the date of randomization until the last day of the study which will be the day all of the patients have had at least one of the following outcomes: 1) Improvement of two points on a seven-category ordinal scale. 2) Discharge from the hospital 3) Death. If any patient dies, we have reached an important secondary outcome. SpO2 Improvement between the last and first day of hospitalization, using pulse-oximetry. Duration of hospitalization from date of randomization until the date of hospital discharge or date of death from any cause, whichever comes first. Incidence of new mechanical ventilation uses from date of randomization until the last day of the study. Please note that we are trying to add further secondary outcomes and this section of the protocol is still evolving.

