IFN-β 1a is currently used for a variety of diseases, including multiple sclerosis, and has been shown to be effective in several dose-dependent clinical trials. Significantly, IFN-β 1a has a strong antiviral activity have shown in previous studies and also has an acceptable safety profile. In a 2003 study, SARS was treated with human interferons and found that IFN-β was 5 to 10 times more effective than other types of interferons and was the best antiviral drug against SARS-CoV (8).

Due to COVID-19 outbreak, the novel nature, astonishing speed of spreading, severe disease, death and limited data, further studies are required to fill this knowledge gap. So we also aim to examine the therapeutic effect of Interferon Beta 1a, compared to Interferon Beta 1b and the usual therapeutic regimen in COVID-19 in patients that have tested positive and are moderately to severely ill.

Since the recent global outbreak of COVID19, extensive attempts were performed to better understand the new virus and its clinical features. Although lots of clinical trials were conducted, key knowledge gaps remain and so far there is not definitive and effective treatment to manage the disease.

Our study introduces a new therapeutic regimen that reduces mortality rates, length of hospital stay (LOHS) and improves clinical symptoms in patients with COVID-19. So the present therapeutic regimen, as a promising solution, could help health care systems to deal with difficulties caused by the COVID-19 pandemic.

Moreover, to the best of our knowledge, this is the first report, investigating the effectiveness of Interferon Beta 1a, compared to Interferon Beta 1b and the usual therapeutic regimen in COVID-19 confirmed cases.

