**Secondary objectives**

The secondary objectives for this study are:

1. To determine and compare the frequency of side effects in three therapeutic arms
2. To determine and compare the average level of oxygen saturation (Sat O2) in three therapeutic arms.
3. To determine and compare the average respiratory rate (RR) in three therapeutic arms
4. To determine and compare the average length of hospital stay in three therapeutic arms
5. To determine and compare the average length of hospital stay in the intensive care unit (ICU) between three therapeutic arms
6. To determine and compare the frequency of 30-days mortality rates between three therapeutic arms
7. To determine and compare the average time to improve clinical symptoms between three therapeutic arms
8. To determine and compare the average SOFA score in three therapeutic arms
9. To determine and compare the average duration of mechanical ventilation use between three therapeutic arms

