**Secondary Outcomes:**

Secondary outcomes include mortality from the date of randomization until day 21, by which all of the patients will have at least one of the following outcomes: 1) A decline of two steps on the seven-step ordinal scale, 2) Hospital discharge or 3) Death; SpO2 improvement defined as the difference between the last and the first recorded measurement during the hospitalization, using pulse-oximetry; length of stay in the hospital until the date of discharge from hospital or death from any cause, whichsoever came first; incidence of new mechanical ventilation uses from the date of randomization until day 21. Follow-ups of discharged patients will be done utilizing telemedicine visits, online, or over the telephone.

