## **Statistical Methods**

Statistical analysis will be performed by R version 3.6.1 software. The total sample size was calculated according to the Latouche and colleagues approach for estimating sample size in survival analysis with 80% power, alpha=0.05, Hazard Ratio (HR) of 3.0 (as the ratio of the hazard rates of time to clinical improvement (TTCI) corresponding to the intervention group compared to the control group) and assuming that 80% of patients would reach the primary outcome (10). The calculations will be carried out using Package ‘powerSurvEpi’ in R and accounted for a dropout

rate of 15%. Overall 60 patients, will be needed for the study, 20 for each arm.

Frequency rates and percentages will be used for categorical variables, and Interquartile Ranges (IQRs) and median will be used for continuous variables. Kruskal-Wallis test will be used for comparing the continuous variables. The Wilcoxon signed-rank test will compare the before and after intervention effects. Moreover, Chi-Square test will compare the frequency of categorical variables. We will use Kaplan–Meier to analyze the TTCI (compared with a log-rank test).

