# **RESTRICTIONs**

Our study has several limitations. The trial will be open-label and without a placebo-control group, which opens the possibility for risks of bias. Our trial will be carried out in a limited resource setting, where we have no access to the follow-up RT-PCT testing and quantitative Real-Time RT-PCR; therefore, therefore we could not determine the time to a negative RT-PCR test and the viral loads to shed further light on the effect of the studied drugs on viral dynamics. Finally, we will only enroll the severe patients with lower probabilities of survival; hence our findings cannot be extrapolated to all COVID-19 patients.

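### Hospital length of stay ends at discharge or death, whichever is first, so a death earlier than the usual discharge ranks as a favourable short stay

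*Protocol*

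**What the plan says.** The body of the protocol (Study Outcomes, Secondary Outcomes) lists "length of stay in the hospital until the date of discharge from hospital or death from any cause, whichsoever came first". The Protocol Summary (Secondary outcomes) has the same rule: "Duration of hospitalization from date of randomization until the date of hospital discharge or date of death from any cause, whichever comes first". The summary starts the clock at randomisation. The body names no start for this outcome.

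Secondary objective 4 is "To determine and compare the average length of hospital stay in three therapeutic arms". Statistical Methods says that "Kruskal-Wallis test will be used for comparing the continuous variables", with medians and interquartile ranges as summaries. Length of stay is not named there, but it is a continuous variable and no other method is given for it.

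The Background says that the regimen "reduces mortality rates, length of hospital stay (LOHS) and improves clinical symptoms", so a shorter stay is to be read as benefit. The section on restrictions says that "we will only enroll the severe patients with lower probabilities of survival", so some deaths are to be expected. Nowhere does the protocol rank death as worse than discharge for this outcome, limit the outcome to survivors, or treat death as a competing event for it.

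**The concern.** Under the stated rule, a patient who dies on day 3 has a stay of 3 days and a patient who goes home well on day 10 has a stay of 10 days. The rank test places the death on the favourable side. If one arm has more early deaths, its stays look shorter for that reason alone, and a reader following the Background would count this as a gain. The outcome mixes two events of opposite meaning, so a difference between arms cannot be read as faster recovery or as harm without knowing who died and when.

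**Working it through.** **Figures in the protocol.** There is no planning figure for length of stay. The sample size is for the primary outcome and reproduces. For one pair of arms, with hazard ratio 3.0, 80% power and two-sided alpha 0.05, the Schoenfeld formula gives 4 × (1.960 + 0.842)² / (ln 3)² = 26.01, so 27 events. Then 27 / 0.80 = 33.75, so 34 patients, and 34 / 0.85 = 40, or 20 per arm and 60 for three arms. Nothing below changes this.

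**Assumed inputs.** Mortality, day of death and survivors' stay are all assumptions, because the protocol states none of them. Only the 20 patients per arm come from the protocol.

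**Exact example.** Let every survivor go home on day 12, with 4 deaths among 20 in one arm and 8 among 20 in the other.
- Deaths on day 4: (4×4 + 16×12)/20 = 10.4 days vs (8×4 + 12×12)/20 = 8.8 days. The arm with twice the deaths looks shorter.
- Deaths on day 10: 11.6 vs 11.2 days.
- Deaths on day 14: 12.4 vs 12.8 days. The order reverses.

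**General form.** With survivors' mean stay S, mean day of death D (both the same in each arm) and mortality m₁ and m₂, the mean stay in an arm is (1 − m)S + mD. The apparent shortening in arm 2 is therefore (m₂ − m₁)(S − D). With S = 10, m₁ = 0.20 and m₂ = 0.40 this is 0.2 × (10 − D): 1.2 days at D = 4, 0.6 at D = 7, 0 at D = 10 and −0.8 at D = 14.

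**Simulation of the same case.** Two arms of 20; survivors' stay gamma with shape 4 and mean 10 days; time to death gamma with shape 3 and mean D; mortality 20% vs 40%; Mann-Whitney test at 0.05; at least 3,000 trials per row.

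| Mean day of death | More lethal arm has the shorter mean stay | Significantly shorter |
|---|---|---|
| 4 | about 76% | about 13% |
| 7 | about 64% | about 6% |
| 10 | about 50% | about 2.5% |
| 14 | about 35% | about 1% |

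With no bias, these columns would read about 50% and 2.5%. At day 4 the median stays are about 8.0 vs 6.5 days. With mortality of 20% vs 60% and deaths at mean day 4, the more lethal arm is shorter in about 93% of trials and significantly shorter in about 38%.

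**Three arms, Kruskal-Wallis.** With survivors' mean stay about 12 days and mortality 40%/20%/20%:
- deaths at mean day 5: medians about 8.5, 10.2 and 10.1 days, with rejection in about 11% of trials;
- deaths at mean day 12: 11.4, 11.6 and 11.5 days;
- deaths at mean day 16: 12.6, 12.1 and 12.1 days, so the more lethal arm now looks longer.

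**Does the repair work?** With hospital-free days to day 21 and deaths scored 0, in the two-arm case with deaths at mean day 4, the more lethal arm looks better in about 13% of trials at 20% vs 40% mortality and about 1% at 20% vs 60%. A death scores 0 on whatever day it occurs, so its timing no longer enters.

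**The case against.** The strongest reply is that little hangs on this outcome. It is one of several secondary outcomes. The primary outcome does not count death as improvement. Mortality to day 21 is reported beside length of stay, so an attentive reader could spot the artefact. This stands as an argument about severity. It does not correct the score, and with 20 per arm a real difference in mortality may go undetected.

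A second reply is that the size rests on assumed timing. That is right. A reader might infer that the more lethal arm will generally look better; the protocol does not support this. It gives no time of death, and the bias vanishes or reverses once deaths come as late as discharges or later. Even with early deaths, a doubling of mortality gives a significant false advantage in only about 13% of trials.

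A reader might also take the planning assumption that 80% reach the primary outcome as an implied 20% mortality. It is a sample-size input, and the protocol does not present it as a death rate.

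Finally, a reader might extend the fault to ICU stay (objective 5) and to objective 9, "To determine and compare the average duration of mechanical ventilation use between three therapeutic arms". The protocol defines neither duration and does not say how deaths count there. The same problem is possible, but it is not written into the protocol as it is for hospital stay.

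**Conclusion.** The point holds for hospital length of stay. The definition is fixed in two places of the protocol, so it is not a detail left to a statistical analysis plan. It makes death equivalent to discharge alive, and the direction of any resulting bias depends on when deaths occur: towards the more lethal arm if they precede typical discharge, absent if they coincide with it, and against that arm if they follow it. Under the assumptions above (survivors' mean stay 10 days, mortality 20% vs 40%), the more lethal arm is shorter in between about 76% of trials (deaths at mean day 4) and about 35% (mean day 14). The logic is certain; the size is illustrative. This should be fixed. To call it essential would overstate it, since the primary outcome and the sample size of 60 are untouched and mortality is reported separately.

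**What to change.** In both the Protocol Summary and the body, replace length of stay with one of these:
- hospital-free days from randomisation to day 21, with deaths by day 21 scored 0; or
- time from randomisation to discharge alive, with patients who die kept as never discharged through day 21.

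State randomisation as the start of the clock in both places. If ICU stay and ventilation duration are analysed, score them in the same way, as ICU-free and ventilator-free days to day 21 with deaths as 0, and say so.

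The cost is rewording and recoding. Dates of discharge and death are already needed, and the planned remote follow-up of discharged patients can supply their status to day 21. No extra patients are required. The drawback is that free days are slightly less familiar than raw days. Raw stay can still be described separately for survivors and for those who died.

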# **STUDY DESIGN**

**General**

This is a single center, open label, randomized, controlled, parallel group, clinical trial that will be conducted at Loghman Hakim Medical Education Center in conjunction with Shahid Beheshti University of Medical Sciences.

Eligible patients with confirmed SARS-Cov-2 infections will be randomly assigned in a 1:1:1 ratio to one of the three following therapeutic regiments: 1) IFNβ1a (Recigen) (Subcutaneous injections of 44μg (12,000 IU) on days 1, 3, 6) + Hydroxychloroquine + Lopinavir/Ritonavir (Kaletra) [IFNβ1a group], 2) IFNβ1b (Ziferon) (Subcutaneous injections of 0.25mg (8,000,000 IU) on days 1, 3, 6) + Hydroxychloroquine + Lopinavir/Ritonavir (Kaletra) [IFNβ1b group], and 3) Hydroxychloroquine (Single dose of 400 mg on day 1, orally, in all three arms) + Lopinavir/Ritonavir (Kaletra) (400mg/100 mg twice a day for 10 days, orally, in all three arms) [control group]. All three groups will receive standards of care consisting of the necessary oxygen support, non-invasive, or invasive mechanical ventilation.

Patients will be randomly allocated to three therapeutic arms using permuted, block-randomization to balance the number of patients allocated to each group. The permuted block (three or six patients per block) randomization sequence will be generated, using Package ‘randomizeR’ in R software version 3.6.1. and placed in individual sealed and opaque envelopes by the statistician. The investigator will enroll the patients and only then open envelopes to assign patients to the different treatment groups. This method of allocation concealment will result in minimum selection and confounding biases.

The present research is open-label (no masking) of patients and health care professionals who are undertaking outcome assessment of the primary outcome - time to clinical improvement.

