## **Efficacy Assessments**

**Study Outcomes**

**Primary Outcome:**

Our primary outcome measure will be TTCI, defined as the time from enrollment to discharge from the hospital or a decline of two steps on the seven-step ordinal scale; Which so ever came first. Originally introduced by Beigel and colleagues in a posthoc analysis of an influenza study as a six-step ordinal scale, and currently recommended by the WHO R&D Blueprint Team (Accessed May 15, 2020, at https://www.who.int/teams/blueprint/covid-19.) for COVID-19 studies as a nine- step ordinal scale, the utilized seven-step ordinal scale consists of the subsequent categories: (I) Not hospitalized, and has no activity limitations; (II) Not hospitalized, but has activity limitations; (III) Hospitalized, but does not need any supplemental oxygen; (IV) Hospitalized, and needs supplemental oxygen; (V) Hospitalized, and needs either High-Flow Nasal Cannula (HFNC) or non-invasive ventilation; (VI) Hospitalized, and needs invasive ventilation; and (VII) Dead (9).

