## **Inclusion Criteria**

- Age ≥ 18
- COVID-19 Confirmed Cases by Means of RT-PCR
- Oxygen saturation (SPO2) ≤ 93% OR respiratory rate ≥ 24
- At least one of the following: Calibrated contactless infrared forehead thermometry temperature of ≥37.8, cough, sputum production, nasal discharge, myalgia, headache or fatigue on admission.
- Time of onset of the symptoms should be acute (Days ≤ 14)

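### Length of stay has no stated start in the protocol body, and the SpO2 baseline is tied to the hospital stay rather than to randomisation

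*Protocol*

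**What the plan says.** Length of stay appears in three places. The Protocol Summary (Secondary outcomes) starts it at randomisation: "Duration of hospitalization from date of randomization until the date of hospital discharge or date of death from any cause". The Study Design section (Secondary Outcomes) gives only the end: "length of stay in the hospital until the date of discharge from hospital or death from any cause". Item 4 of the Secondary objectives names the average hospital stay and gives no start.

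SpO2 improvement is the last minus the first pulse-oximetry reading of the hospital stay in the Study Design section, and last versus first hospital day in the Protocol Summary. Neither refers to randomisation.

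For mortality and new mechanical ventilation, the Study Design section does name the randomisation date as the start, in the same sentence that leaves it out for length of stay. The primary outcome is "defined as the time from enrollment to discharge from the hospital" or a two-step decline on the ordinal scale. Under General, the order of events is: "The investigator will enroll the patients and only then open envelopes".

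Entry requires "COVID-19 Confirmed Cases by Means of RT-PCR", and the qualifying symptoms are those present on admission. The protocol does not say how long after admission patients are randomised. Statistical Methods plans Kruskal-Wallis tests for continuous variables and a Wilcoxon signed-rank test for before-after effects.

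**The concern.** Treatment cannot affect what happened before allocation. If length of stay is counted from admission, each patient's total includes days that carry no information about the regimens. If the SpO2 baseline is the first hospital reading, any change between admission and allocation becomes part of the measured improvement.

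Two things are at stake. The first is precision in arms of 20, where avoidable noise is costly. The second is the signed-rank test. It compares patients with themselves, so any recovery before the first dose would count as an intervention effect. An SpO2 of 93% or below is one of two alternative entry criteria, so for some patients the first reading may also have been selected for being low.

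The protocol also fixes one named outcome in two ways. An analyst working from the body alone could build a different variable from one working from the summary.

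**Working it through.** **1. Starting points side by side**

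| Outcome | Protocol Summary | Study Design section |
|---|---|---|
| Time to clinical improvement | none stated | enrolment |
| Mortality | randomisation | randomisation |
| New mechanical ventilation | randomisation | randomisation |
| Length of stay | randomisation | none stated |
| SpO2 improvement | first hospital day | first hospital reading |

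Only the last two rows leave room for a start clearly before allocation. For the primary outcome, opening the envelope is the next step after enrolment, and no interval between them is stated.

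**2. The plan's own figure**

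Inputs from Statistical Methods: hazard ratio 3.0, 80% power, alpha 0.05 (taken as two-sided), 80% of patients with the event, 15% dropout.

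- Events for one pair of arms: (1.960 + 0.842)² / (0.25 × (ln 3)²) = 26.01
- Patients: 26.01 / 0.80 = 32.5, so 33
- With dropout: 33 / 0.85 = 38.8, so 39; that is 20 per arm and 60 in three arms

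The stated 60 reproduces. With 40 patients per pair, expected events are 40 × 0.85 × 0.80 = 27.2 and power is 81.7%. No start date enters this calculation, so a common start leaves it unchanged.

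**3. Length of stay if counted from admission**

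Write the whole stay as G + S, where G is the wait before randomisation and S the stay after it. If G is independent of S and has the same distribution in each arm, the mean difference between arms is unchanged and the variance rises from SD(S)² to SD(S)² + SD(G)². The information lost on a difference in means is 1 − SD(S)² / (SD(S)² + SD(G)²). Neither SD is in the protocol; these are assumed ranges:

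| SD of S (days) | SD of G = 1 | SD of G = 2 | SD of G = 3 |
|---|---|---|---|
| 4 | 6% | 20% | 36% |
| 6 | 3% | 10% | 20% |
| 8 | 1.5% | 6% | 12% |

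For example, with 6 and 3: 1 − 36/45 = 0.20.

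The planned test is rank-based, so a simulation is closer to the plan. Assumptions: 20 per arm; gamma-distributed S with shape 2, rounded up to whole days, mean 6 days in each interferon arm and 10 in control; Poisson wait with the same mean in every arm; Kruskal-Wallis at 0.05; 4,000 trials per setting. Type I error uses mean 10 in all arms.

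| Mean wait (days) | Power | Type I error |
|---|---|---|
| 0 | 52% | 4.8% |
| 1 | 52% | 4.6% |
| 2 | 49% | 4.8% |
| 3 | 47% | 4.3% |
| 5 | 45% | 4.9% |

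Simulation error on the power figures is about √(0.5 × 0.5 / 4000) = 0.8 percentage points. The loss is modest and the error rate holds.

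**4. Chance imbalance in the wait**

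The standard error of a difference in mean wait between two arms of 20 is SD(G) × √(2/20): 0.32, 0.63 and 0.95 days for SDs of 1, 2 and 3. A 1-day imbalance is therefore 3.2, 1.6 or 1.1 standard errors. The test's error rate already allows for imbalance of this kind.

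**5. SpO2**

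Last minus first reading = (last − value at randomisation) + (value at randomisation − first reading). The second bracket is pre-treatment change. Between arms it has the same expectation, so it adds noise and no systematic difference. Within an arm its expectation need not be zero, and a signed-rank test on the total would attribute it to treatment. The protocol gives no figure from which to size it.

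**The case against.** The best defence is that the Protocol Summary already supplies the start for length of stay. The body omits it but does not state a different one, so reading the two together gives randomisation. Nor does the protocol say that patients wait in hospital for the RT-PCR result; confirmation could precede admission, and the gap could be nil. Both points stand as limits on size. They do not remove the inconsistency, because the body names the randomisation date for the outcomes on either side of length of stay and leaves it out there. The defence also does not reach SpO2, whose baseline is tied to the hospital stay in both places.

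A reader might infer that pre-randomisation days enter the treatment comparison generally, the primary outcome included. The protocol does not support that. Mortality and new ventilation start at randomisation, and the primary starts at enrolment, directly before the envelope is opened.

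A reader might also fear that an admission reading could serve as the baseline for the two-step decline. The ordinary reading of a time that runs from enrolment is a decline from the category at enrolment, and the choice of charted value is detail that a statistical analysis plan commonly settles.

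Finally, a reader might see bias between arms. Randomisation balances the wait in expectation, so that does not follow.

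**Conclusion.** The point holds for two secondary outcomes and is minor. Length of stay is defined with a start in one place and without one in another. The SpO2 baseline can precede allocation under either definition.

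The between-arm consequence is lost precision, conditional on a gap between admission and randomisation that the protocol does not give. In the simulated scenario it is 3 percentage points of power at a mean wait of 2 days and 7 at 5 days; the 52% starting value belongs to that scenario and is not an estimate of the trial's power. The within-arm consequence is potentially more serious, but arises only if the signed-rank test is applied to SpO2, which the protocol does not specify.

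**What to change.** - In the Study Design section, start length of stay at the date of randomisation, as the Protocol Summary already does, and carry that into item 4 of the Secondary objectives.
- In both the Protocol Summary and the Study Design section, define baseline SpO2 as the last value recorded at or before randomisation.
- For consistency only, start the primary outcome at randomisation instead of enrolment.

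The cost is a few words. The randomisation date is necessarily held, and Safety Assessments already provides for daily monitoring of vital signs. The sample size does not change. The new SpO2 baseline removes pre-treatment change from a before-after test, but not natural recovery after allocation, so treatment conclusions on SpO2 should still rest on the comparison between arms.

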## **Study Drugs**

- **Hydroxychloroquine:**

400mg bid for first day then 200mg bid for 10 days

- **lopinavir/ritonavir (Kaletra):**

400mg/100mg bid for 10-14 days

For those that could not get orally:

5-ml suspension bid for 10-14 days

- **Interferon beta-1a:**

SC injection 44 micro-gram for 3 days (on days 1,3,6)

- **Interferon beta-1b:**

SC injection 0.25 mg for 3 days (on days 1,3,6)

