## **Exclusion Criteria**

- Refusal to participate expressed by patient or legally authorized representative if they are present
- Patients with prolonged QT or PR intervals, Second or Third Degree heart block, Arrhythmias including torsade de pointes
- Patients using drugs with potential interaction with Hydroxychloroquine + Lopinavir/Ritonavir, Interferon-β 1a، Interferon-β 1b.
- Pregnant or lactating women.
- History of alcohol or drug addiction in the past 5 years.
- Blood ALT/AST levels > 5 times the upper limit of normal on laboratory results.

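### New mechanical ventilation scores death without ventilation as event-free and names no at-risk population; average ventilation duration has a related flaw

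*Protocol*

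**What the plan says.** **Outcome.** Under Study Design, Secondary Outcomes, the protocol lists "incidence of new mechanical ventilation uses from the date of randomization until day 21". The Protocol Summary gives the same outcome a different end: "Incidence of new mechanical ventilation uses from date of randomization until the last day of the study". Neither place states a denominator or says how a death before ventilation is scored.

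**Entry.** The severity criterion is "Oxygen saturation (SPO2) ≤ 93% OR respiratory rate ≥ 24". None of the six exclusions concerns respiratory support at baseline, and neither does the eligibility paragraph in the Protocol Summary.

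**Care and scale.** The General section states: "All three groups will receive standards of care consisting of the necessary oxygen support, non-invasive, or invasive mechanical ventilation". The seven-step scale puts non-invasive ventilation, together with high-flow oxygen, in category V, invasive ventilation in VI and death in VII.

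**Analysis.** Statistical Methods gives one generic test for categorical variables, a chi-square comparison of frequencies.

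**Duration.** Secondary objective 9 reads: "To determine and compare the average duration of mechanical ventilation use between three therapeutic arms". It does not say whether the average covers all patients or only those ventilated, or how patients who die enter it.

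**The concern.** A count of new ventilation is meant to show whether a regimen prevents deterioration. It does so only if everyone counted could have the event and if a worse result cannot be scored as a better one.

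The second condition fails on the text. Death without ventilation is the worst result on the protocol's own scale, yet in a plain table of ventilated against not ventilated it falls in the favourable cell. An arm with more such deaths can look better on this outcome.

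The first condition is not secured. A patient in category VI at randomisation is eligible and cannot have a new event. If such patients are kept in the denominator, they dilute the incidence and flatter an arm that happened to start sicker.

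Objective 9 has the same weakness. A ventilated patient who dies early contributes a short duration, which reads as favourable. Averaging only over ventilated patients compares subsets selected after randomisation: a regimen that spares the milder patients ventilation leaves only the sickest in its average.

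**Working it through.** **The plan's own figure.** The protocol gives no expected rate or sample size for the ventilation outcome. Its total of 60 rests on time to clinical improvement and reproduces: a hazard ratio of 3.0, 80% power and alpha 0.05 (taken as two-sided) need 27 events. Then 27/0.80 = 33.75 patients for two arms, and 33.75/0.85 = 39.7, which is 20 per arm and 60 for three arms. This does not bear on the present point beyond fixing the arm size.

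**Inputs for the illustration.** The arm size of 20 is from the protocol. The numbers ventilated at entry, newly ventilated and dying unventilated are assumptions, because the protocol gives none of them.

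**Step 1: death without ventilation.** One patient in an arm of 20 is 1/20 = 5 percentage points. Suppose 6 of 20 are newly ventilated:

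| Deaths without ventilation | Ventilation only | Ventilation or death |
|---|---|---|
| 0 | 6/20 = 30% | 6/20 = 30% |
| 1 | 30% | 7/20 = 35% |
| 2 | 30% | 8/20 = 40% |
| 3 | 30% | 9/20 = 45% |
| 4 | 30% | 10/20 = 50% |

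The ventilation count stays at 30% while 0 to 20 points of deaths go unseen in it. The order of two arms can even reverse. Take 6 ventilated and no unventilated deaths in one arm, and 4 ventilated and 4 unventilated deaths in the other. Ventilation alone is 30% against 4/20 = 20%, but ventilation or death is 30% against (4+4)/20 = 40%.

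**Step 2: patients ventilated at entry, if the denominator is all 20.** With risk p among those at risk and v ventilated at entry, the all-patient incidence is p(20 − v)/20. For p = 40%:

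| v | All-patient incidence |
|---|---|
| 0 | 40% |
| 2 | 0.40 × 18/20 = 36% |
| 4 | 0.40 × 16/20 = 32% |
| 6 | 0.40 × 14/20 = 28% |

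As an example of imbalance between arms, take p = 30% in both, with 4 ventilated at entry in one and 1 in the other: 0.30 × 16/20 = 24.0% against 0.30 × 19/20 = 28.5%. That is a gap of 4.5 points with no true difference.

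**Step 3: does restricting the denominator cure both problems?** It removes Step 2 but not Step 1. With 4 of 20 ventilated at entry, 16 are at risk, and each unventilated death is still scored as event-free, now worth 1/16 = 6.25 points.

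**Step 4: the windows.** The design section ends at day 21. The Protocol Summary ends when every patient has improved by two points, been discharged or died. The design section assumes that this state is reached by day 21, but the two rules give different dates if it is reached earlier or later.

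**The case against.** The strongest reply is that the protocol does not say this outcome is counted over all patients. A reader might infer that it is, and conclude that already-ventilated patients certainly score as favourable. The text does not support this: no denominator appears anywhere, and incidence of a new event can equally mean a count among those not ventilated at randomisation. On that reading Step 2 falls away. The at-risk set, and whether non-invasive ventilation counts, are also details that a statistical analysis plan could settle, and that plan is not at hand. This stands, so the denominator is raised here only as a possibility.

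Two further inferences should be resisted. The mention of limited resources under RESTRICTIONs concerns access to PCR testing, so it is no evidence of a ventilator shortage; the General section promises necessary ventilation in all arms. The suspension "For those that could not get orally" may serve patients with swallowing difficulty or those intubated after randomisation, so it does not show ventilation at entry.

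It is also fair that mortality is listed over the same 21 days, so deaths are not lost to the trial. Baseline imbalance under randomisation is a matter of chance, and the 4.5-point gap in Step 2 is only 0.9 of a patient (0.045 × 20). Neither reply answers Step 1. A separate mortality figure does not correct the ventilation comparison, and it does not tell a reader how many of the deaths occurred without ventilation. Deaths may also differ between arms because of treatment, not only by chance.

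**Conclusion.** The point holds in a limited form. Taken as written, the outcome and its chi-square comparison score death without ventilation as freedom from ventilation. Patients invasively ventilated at entry are eligible, cannot have the event and, with no stated denominator, may be scored the same way. Objective 9 is open to distortion by death and, if averaged over ventilated patients only, by selection after randomisation.

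The size is illustrative: 5 percentage points per unventilated death in an arm of 20 and, if all patients are counted, 4 to 12 points of understatement for 2 to 6 of 20 ventilated at entry at an assumed 40% risk. Nothing in the protocol shows how often either situation would arise or which arm it would favour. The primary outcome and the sample size are not affected. The protocol itself expects to enrol severe patients with reduced chances of survival, so deaths are foreseeable and a definition that copes with them is worth having.

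**What to change.** 1. Define the outcome as new invasive ventilation (category VI) or death by day 21, among patients not in category VI at randomisation. Report the two components separately beside the composite. Naming category VI also settles whether non-invasive ventilation counts.
2. Replace or supplement objective 9 with days alive and free of invasive ventilation to day 21 in all randomised patients, with death by day 21 scored 0.
3. Change the window in the Protocol Summary to day 21 so that it agrees with the design section.

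The cost is small. The category at entry is needed for the primary outcome, vital status to day 21 is needed for mortality, and ventilation start and stop dates are already needed for the present outcome and objective 9. The protocol should say that those dates are recorded, since its daily monitoring paragraph does not name them. The downsides are a composite that overlaps with the mortality outcome, which is why its components must be shown, and, if objective 9 is replaced and not supplemented, a change in what that objective measures.
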